## Abstract

**Background:**

Smoking cessation is the most effective means of slowing the decline of lung function associated with chronic obstructive pulmonary disease (COPD). While effective smoking cessation treatments are available, they are underutilized and nearly half of people with COPD continue to smoke. By addressing both nicotine and behavioral dependence, electronic cigarettes (EC) could help people with COPD reduce the harm of combustible cigarettes (CC) through reductions in number of Cigarettes per Day (CPD) or quitting CC completely. The purpose of this pilot study is to identify barriers and facilitators to the use of and assess the preliminary effectiveness of EC as a harm reduction strategy among people with COPD.

**Methods:**

In an open-label two-arm randomized controlled trial pilot study, 60 patients identified as smokers with a COPD diagnosis via electronic health records from a large urban health center are randomized in a 1:1 ratio to either standard care [counseling + nicotine replacement therapy (NRT)] or counseling + EC. The NRT arm will receive nicotine patches and nicotine lozenges for 12 weeks. The EC arm will receive EC for 12 weeks. Both cohorts will receive counseling from a licensed mental health counselor. Using ecological momentary assessment, participants will report their use of CC in both arms and EC use in the EC arm daily via text message. Primary outcomes will be feasibility and acceptability of intervention, and secondary outcomes will be reduction in CPD and change in COPD symptoms as measured by COPD Assessment Tool (CAT) score at 12-weeks. EC displacement of CC. To explore attitudes towards the use of EC as a harm-reduction strategy for patients with COPD, interviews will be performed with a sample of participants from both study arms.

**Discussion:**

Despite decades of availability of smoking cessation medications, nearly half of people with COPD still smoke. This study aims to address the unmet need for feasible and effective strategies for reducing CC use among those with COPD, which has the potential to significantly improve the health of people with COPD who smoke.

*Trial Registration* ClinicalTrials.gov Identifier: NCT04465318.

## Introduction

Despite considerable progress, smoking remains the leading preventable cause of death in the United States (US), causing 480,000 deaths and $300 billion in health-related economic losses each year [1]. In the US, chronic obstructive pulmonary disease (COPD) represents one fifth of all smoking-related deaths [2] and over 16 million people in the US have COPD [3]. Globally, the burden of COPD is even greater, with COPD projected to be the third largest cause of death by 2030 [4].

Among those with COPD who smoke, smoking cessation is the most effective means of slowing the decline of lung function and overall disease progression [5, 6]. Patients at all stages of COPD benefit from smoking cessation [6]. Although effective smoking cessation treatments are available, after an initial quit relapse is high [7] and nearly half of smokers with COPD are still smoking [8]. To encourage more patients with COPD to quit, alternate smoking cessation tools are needed.

By addressing both nicotine and behavioral dependence, electronic cigarettes (EC) may represent a more appealing alternative smoking cessation tool for many smokers [9–11], and when paired with behavioral therapy were shown to be nearly twice as effective in helping people quit smoking (18.0% vs. 9.9%) as other nicotine replacement therapies (NRT) [12]. While not all EC smoking cessation studies have shown higher quit rates, there is moderate‐certainty in the evidence that quit rates are higher in people randomized to nicotine EC than in those randomized to nicotine replacement therapy (NRT) [13]. Switching from combustible cigarettes (CC) to EC has been associated with improved lung function in patients with COPD [14, 15]. FDA-approved smoking cessation medications have been less effective for patients with COPD [16]. This may be because pharmacotherapy interventions do not replace the behavioral ritual associated with CC use, nor deliver nicotine as rapidly as CC [17, 18].

Switching to EC may be beneficial in people with COPD. Little is known about health consequences of EC use among smokers with COPD [19] Polosa and colleagues (2016) conducted a retrospective chart review of 48 patients with COPD who had reported regular daily use of ECs on at least two follow-up visits at 12-, 24-, 48-, and 60-months. Compared to regularly smoking COPD patients, switching from CC to EC was associated with improved lung function [14] and benefits persisted long-term [15, 20]. At 60-month follow-up, people who switched to EC had a significant decrease in COPD exacerbations (from 2.3 to 1.1) and in scores on the COPD assessment tool (from 21.5 to 17.5). People who switched to EC had significant and constant improvement in lung function compared to continued smokers at all follow-up time points.

EC are not risk free and are undeniably harmful to non-smokers [21, 22]. Nevertheless, evidence suggests the benefits of EC in helping with CC cessation and harm reduction substantially outweigh their potential harms [18, 23, 24]. A harm reduction approach seeking to achieve switching from CC to EC may be a more pragmatic approach than complete nicotine abstinence for those with high levels of addiction thus making EC use particularly appropriate for patients with COPD who continue to smoke [25]. Those with COPD could reduce CC harm by reducing the number of cigarettes per day (CPD) or completely switching to EC. The overarching goal of this study is to address the unmet need for feasible and efficacious strategies for reducing CC use among those with COPD, which has the potential to significantly improve the health of those with COPD who smoke.

This study aims to collect information on the feasibility and acceptability of an EC harm-reduction intervention among those with COPD who smoked. It also seeks to explore the preliminary effectiveness of the intervention on reduction of CPD and improved respiratory health.

## Methods

In conjunction with a qualitative study using in-depth interviews with 20 study participants, the proposed study seeks to conduct an open-label randomized controlled trial (RCT) comparing the effect of standard care (NRT + counseling) to EC + counseling on reduction of CPD in 60 smokers with COPD. Specifically, this study aims to: (1) determine the feasibility and acceptability of an EC intervention for CC harm reduction among a COPD population; (2) estimate EC-related reduction in CPD 12 weeks post baseline; (3) measure engagement with the text-messaging-based smoking diary; and (4) estimate the effect of EC on reductions in COPD symptoms. Aims examining intervention effect are exploratory as the study is not powered to detect significant differences in results. The study protocol has been approved by the NYU Langone Institutional Review Board (IRB).

The primary hypothesis to be tested is: EC is a feasible and acceptable harm-reduction intervention among patients with COPD who smoke. Secondary hypotheses include: (1) An EC harm-reduction intervention will be more effective than NRT in reducing CPD in patients with COPD who smoke; and (2) An EC harm-reduction intervention will be more effective than NRT in reducing COPD symptoms in patients with COPD who smoke.

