### Trial design

After completing the baseline survey on tobacco use, physical health, and mental health, we will use a two-arm study design to randomize 60 patients to counseling + NRT (standard care) or counseling + EC. Participants will receive four counseling sessions in 12 weeks; each session will follow a study visit monitoring any physical or mental changes and side effects from using NRT or EC. All participants will complete a follow-up survey at 24 weeks (Fig. 1). During the 12 weeks of study participation, participants will report their tobacco use daily by responding to automated text messages serving as a smoking diary. We will also invite 20 participants for an in-depth interview on their study experience, outcome expectations, EC perceptions, and barriers to smoking cessation.

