#### Randomization

After eligibility screening, participants will be randomized into one of the two study arms (EC or NRT; ratio 1:1) using minimization methodology. This approach has been found to achieve significantly better covariate balance than other randomization methods with a small sample size [30]. Randomization will be stratified by three key variables CAT score (10–19 and ≥ 20), CPD (< 20 and ≥ 20), and sex and will occur using a REDCap based system which includes verification of eligibility criteria prior to the assignment of a study ID and intervention group. Due to the nature of the study, participants are not blind to their randomization allocation.

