This study is not meant to provide a definitive test of intervention efficacy and will be used to inform future sample sizes for a larger trial [48, 49]. In the primary analysis the sample size is anticipated to provide 80% power to detect a difference of 0.73 points in intervention satisfaction between study arms. For other primary measures, the sample size is anticipated to provide exploratory results to examine observed trends, but not statistically significant difference. For secondary analyses of effectiveness, in a Poisson generalized linear model for the number of CC reduced from baseline to follow-up, we will have greater than 90% power to detect a rate ratio of RR = 1.60 (e.g., a reduction by 5 CC per day in the NRT condition vs. 8 in the EC condition). If there is marked overdispersion of the number of CC per day reduced (κ = 0.2), we will still have greater than 80% power to detect RR = 1.80 (e.g., 5 vs. 9 CC per day reduction). Similarly, without considering covariates, we have 80% power to detect a difference of at least 2.7 on the CAT score, and with effective covariates, we have 80% power to detect a difference of 2.2. Translated to standardized mean differences, these are modest effects (d = 0.33 and d = 0.26). In secondary analyses, we will consider CPD collected daily over a 14-day period prior to the end of the 12-week follow-up. This will increase the power by increasing sample size providing for greater than 90% power to detect a rate ratio of RR = 1.20 (e.g., a reduction by 5 CC per day in the NRT condition vs. 6 in the EC condition). If there is marked overdispersion of the number of CC per day reduced (κ = 0.2), we will still have greater than 80% power to detect RR = 1.40 (e.g., 5 vs. 7 CC per day reduction).

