Our study protocol has a few limitations. First, as a pilot study the protocol is not powered to detect small differences in CPD or CAT Scores between the NRT and EC arms. Second, CAT Score is not the gold standard for the assessment of respiratory health. If this study is successful, future research needs to include assessment of airflow by spirometry, as well as by assessment of small airway function using respiratory oscillometry. While FEV1 change is not typically observable in early stage COPD patients, oscillometry may identify the presence of small airway injury in this population [72]. Adherence to study medications is not directly measured, therefore analyses are limited to intent-to-treat rather than per-protocol. The NJOY EC used in the study is not representative of all EC available and additional research using alternate products is called for. EC contain nicotine, which is an addictive substance and therefore there is potential for participants to continue EC use after the study is complete. The counseling protocol does not include EC cessation. Future research on EC cessation methods and continued EC use after switching is called for. Finally, all study measures are self-report. Future studies should include bio-confirmation of CC reduction such as CO.

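### The protocol calls the EC versus NRT effect comparisons unpowered in one place and 80% to over 90% powered in another; the CAT power claim fails on the protocol's own effect sizes

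*Protocol article*

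**What the plan says.** All references are to the protocol article.

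- **Methods, aims paragraph:** the aims on intervention effect are called exploratory on the ground that "the study is not powered to detect significant differences in results". Lack of power is given as the reason for the exploratory status, without qualification by outcome or effect size.
- **Methods, hypotheses paragraph:** the secondary hypotheses are directional. The first reads "An EC harm-reduction intervention will be more effective than NRT in reducing CPD in patients with COPD who smoke"; the second makes the same claim for COPD symptoms.
- **Statistical methods:** after a disclaimer that the pilot is not a definitive efficacy test, the section says "we will have greater than 90% power to detect a rate ratio of RR = 1.60" for the CPD reduction (5 versus 8 per day). It gives over 80% power at RR 1.80 with κ = 0.2, and 80% power for CAT differences of 2.7 points (no covariates) and 2.2 points (with covariates), equated to d = 0.33 and 0.26 and described as modest. For 14 days of daily reports it claims "greater than 90% power to detect a rate ratio of RR = 1.20", and over 80% at RR 1.40 with κ = 0.2.
- **Discussion, limitations paragraph:** "the protocol is not powered to detect small differences in CPD or CAT Scores".

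**The concern.** Two of these sections speak about the same comparisons and give opposite answers on power, and the third does not reconcile them. Excluding only small differences is narrower than the unqualified statement in Methods. It also sits badly with claimed power at RR 1.20 (5 versus 6 cigarettes) and at d = 0.26.

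A published protocol is the reference against which the results will be judged. With both positions in print, a significant CPD result could be presented as the outcome of a well-powered test, and a null one set aside as unpowered. A reader planning the larger trial could also take from the CAT sentence that 60 patients suffice to detect 2.7 points, which the design cannot do.

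**Working it through.** **Inputs.** Sample size: "two-arm study design to randomize 60 patients". Allocation: "EC or NRT; ratio 1:1", hence 30 per arm; no dropout allowance is stated. Effect sizes, mean reductions and κ are from Statistical methods. The significance level is not stated; two-sided 5% is assumed.

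**Check of the basis.** The same section gives 80% power for 0.73 points in satisfaction. With 30 per arm and SD = 1 (assumed), power is 79.4% by t-test and 80.7% by the normal formula. So 30 per arm at two-sided 5% is very likely the basis the authors used.

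**CAT.** Power ≈ Φ(d/√(2/30) − 1.96), with √(2/30) = 0.258.
- d = 0.33: Φ(1.278 − 1.96) = 24.8%; t-test 24.2%.
- d = 0.26: Φ(1.007 − 1.96) = 17.0%; t-test 16.8%.
- One-sided testing gives only about 35% and 26%.
- If the covariate gain implied by 2.2/2.7 = 0.815 is credited to the residual SD, 2.2 points corresponds to d = 2.2/(8.18 × 0.815) = 0.33, so power returns to about 24–25%.

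The implied SD is 2.7/0.33 = 8.2. The d detectable at 80% power with 30 per arm is 0.74 (t-test), or 0.736 × 8.18 = 6.0 points. For 2.7 points to have 80% power the SD would have to be 2.7/0.736 = 3.7, which contradicts d = 0.33. Reaching 80% at d = 0.33 takes about 145 per arm, and at d = 0.26 about 233.

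Expected 95% CI half-width: 2.00 × 8.2 × 0.258 = 4.2 points unadjusted, and 4.24 × 0.815 = 3.5 with the implied covariate gain. Both exceed the differences called detectable.

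**CPD, single time point.** Power = Φ(ln RR/SE − 1.96), with SE² = [(1/m₁ + κ) + (1/m₂ + κ)]/30.
- 5 versus 8, κ = 0: SE = √(0.325/30) = 0.104; 0.470/0.104 − 1.96 = 2.56; power 99.5%. The stated bound (over 90%) holds.
- 5 versus 9, κ = 0.2: SE = √(0.711/30) = 0.154; 0.588/0.154 − 1.96 = 1.86; power 96.8%. The stated bound (over 80%) holds.
- With 24 per arm (20% loss, assumed) the two figures are 98.1% and 92.7%.
- The result depends on κ: at RR 1.60 power is 85.6% if κ = 0.2, and at RR 1.80 it is 80.3% if κ = 0.5.

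**CPD, 14 daily reports.** Fourteen reports per person multiply the information by 14/(1 + 13 × ICC), where ICC is the within-person correlation. The protocol states none, so the whole range is shown.

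| ICC (assumed) | RR 1.20, Poisson | RR 1.40, κ = 0.2 |
|---|---|---|
| 0 | about 100% | about 100% |
| 0.1 | 98% | about 100% |
| 0.3 | 80% | 95% |
| 0.5 | 61% | 83% |
| 0.8 | 45% | 66% |
| 1 | 38% | 57% |

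The claimed bounds (over 90% and over 80%) hold only for ICC below about 0.20 and 0.55. For RR 1.20, 90% power needs SE = 0.1823/3.242 = 0.0562. The single-report SE is √(0.3667/30) = 0.1106, so (1 + 13 × ICC)/14 may be at most (0.0562/0.1106)² = 0.259, giving ICC ≤ 0.20. The same steps for RR 1.40 (SE 0.3365/2.802 = 0.120 against 0.157) give 0.55.

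**The case against.** The best defence is that the exploratory status is consistent. The power paragraph opens by disclaiming a definitive test of efficacy, the aims speak of estimating effects, and the limitations paragraph calls the study a pilot. Directional hypotheses in a trial labelled exploratory are ordinary. On this view only the wording about power varies, and correcting the CAT figures plus qualifying one sentence in Methods would settle it.

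Much of that stands. The label is clear, the directional hypotheses are not in themselves a fault, and the single-time-point CPD figures need not be deleted. But the disclaimer does not remove the conflict. The same paragraph says the other primary measures will show trends rather than significant differences, then presents CPD and CAT with 80% to over 90% power. That places them on the powered side, where Methods places them on the unpowered side.

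Three stronger readings are tempting and not supported:
- A reader might infer that the protocol pre-writes two opposite interpretations of a null result. It contains no rule for interpreting one; the ambiguity is a consequence of the text, and the disclaimers favour the exploratory reading.
- A reader might infer that a null CPD result would count against a full trial. The Discussion ties the next trial to feasibility and acceptability, not to CPD.
- A reader might set the single-time-point interval for the CPD ratio at κ = 0.2 against RR 1.20 and call the latter undetectable. RR 1.20 is claimed for 14 daily reports without overdispersion, so the two are not comparable. The proper criticism is the missing within-person correlation.

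**Conclusion.** The inconsistency is real, and it resolves differently by outcome. For CAT, Methods is right and the 80% claim is wrong on the protocol's own effect sizes: power is about 24% and 17%, and the detectable difference is about 6 points. For CPD at a single time point, the stated power follows from its inputs, so the unqualified denial of power in Methods is too broad. For the 14-day analysis the claims cannot be verified, and power may be as low as 38% (RR 1.20) and 57% (RR 1.40).

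These results assume 30 analysed per arm, a two-sided 5% level, and an SD taken from the stated d. Dropout would lower the CAT power further. No one-sided, t-test or normal variant brings CAT near 80%. The documents do not support saying that the whole design is unpowered, nor that its exploratory label is absent.

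**What to change.** Keep the exploratory status and use one power statement in Methods, Statistical methods and the limitations paragraph:

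1. Remove the 80% CAT power claim, or replace it with the expected 95% CI half-width (about 4.2 points unadjusted at SD 8.2) or the detectable difference of about 6 points (d = 0.74).
2. Keep the single-time-point CPD figures only as conditional on the Poisson or κ = 0.2 assumption, and qualify the Methods sentence accordingly.
3. Drop the 14-day figures, or state the within-person correlation they assume.
4. State that the CPD and CAT comparisons will be reported as estimates with 95% confidence intervals, and that neither a significant nor a non-significant result will be read as confirming or refuting efficacy.
5. Let the directional hypotheses stay if they are labelled exploratory.

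This is a change of wording, with no effect on patients, data or models. The cost is giving up power statements that look more favourable.

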### Participants

The sample will consist of 60 adults with COPD who smoke. These participants will be recruited from the electronic health record (EHR) of the New York University Langone Health system (NYULH), a private hospital system serving New York, New Jersey, and Connecticut with approximately 6.8 million active patients, including approximately 45,000 with a COPD diagnosis. The prevalence of current smoking among NYULH patients with a COPD diagnosis is 21%, which is about 50% higher than the prevalence of smoking in the general New York City population [26].

#### Inclusion criteria

Potential participants will be included if they (1) have an ambulatory ICD-10 code for COPD in the last 12 months; (2) a COPD Assessment Tool (CAT) [27] score ≥ 10; (3) are aged 21 to 75 years (the legal age for purchasing EC is 21); (4) are a current CC smoker (more than 5 packs in a lifetime; smokes 4 or more days/week); (5) smoke at least 5 CC per day on days they smoke CC; (6) are motivated to quit smoking (at least a 5 on a 10-point Contemplation Ladder [28]); and (7) possess a phone with text messaging capabilities.

#### Exclusion criteria

Potential participants will be excluded if they (1) have a CAT score ≥ 30 (representing severe COPD) [27] or < 10 (representing mild COPD); (2) report using NRT or EC within the last 14 days; (3) have a medical condition (e.g. unstable angina/heart disease) precluding use of nicotine patch or gum as determined by the study physician or by their treating physician; or (4) are pregnant (as determined by urine pregnancy test for women under age 52) or breastfeeding (self-reported). Women of childbearing age must also be willing to use an approved form of birth control during the course of the study if not practicing abstinence. Approved birth control methods include: hormonal birth control (e.g. “the pill”), barrier methods (e.g. condoms, diaphragm), and intrauterine devices (IUDs). Use of birth control will not be directly assessed, however, as required by the IRB, if a participant becomes pregnant during the course of their study participation they will be withdrawn from the study and referred to their personal physician for further smoking cessation advice.

#### Recruitment

Participants will be recruited from a list of CC-smokers with COPD in the NYULH EHR who have not opted out of being contacted for clinical research. Prior to contacting a patient, the treating physician will be notified of their patient’s potential participation in the study. Patients will not be contacted if their physician responds stating that their patient should not participate. Participation will be at the discretion of the treating physician, who will be encouraged, but not required to disclose the reason for exclusion. Potential reasons for exclusion are expected to include severe psychiatric illness or comorbidities where nicotine replacement would be contraindicated.

To reach out to potential participants we will use a multimodal strategy, first sending a mailing and following up with a phone call. Potential participants will receive a letter introducing the study along with the Informed Consent form. For potential participants who have an active MyChart account (an online system that allows patients to access their medical records and communicate with their physicians), we will also send a MyChart message describing the study. One week later, we will call them by telephone to complete the eligibility screening. We will make up to 5 call attempts to each potential participant. Call attempts will be made over a span of two weeks and be scheduled at varying days of the week and times of day. Eligible participants will be invited to give informed consent digitally via the REDCap (Research Electronic Data Capture) e-Consent Framework, a secure web application for building and managing online surveys and databases [29].

